## Abstract

**Aim:**

The aim of this study is to report a trial protocol for assessing the improvement of older adults’ well-being, promoting active and healthy aging, and reducing the risks of social exclusion, using a virtual coach.

**Background:**

Increased longevity brings with it reduced autonomy and independence, and it is therefore necessary to act with preventive measures that can promote active and healthy aging. With the development of technology, new tools have appeared, including virtual coaches, which can enable people to lead a healthy lifestyle by identifying individual needs and goals and providing personalized recommendations and advice. However, it is important that these coaches take into consideration the inter-individual and cross-cultural differences of each person.

**Design:**

A randomized controlled trial is proposed.

**Methods:**

This study will recruit 240 healthy subjects aged 65 years and older. Participants will be assigned to an experimental group that will receive the e-VITA system or to the control group that will receive an information booklet only. The primary outcome measure is the person's quality of life (QoL). Data will be collected at baseline, 3 months after the trial, and at the end of the trial, after 6 months.

**Discussion:**

This study will evaluate the effectiveness of the e-VITA system, consisting of a virtual coach, several sensors for monitoring, a smartphone for use at home, and a booklet, in improving the older person's quality of life. The increased perceived well-being will also be linked to improvements in other areas of the person's life, psychological and cognitive status, the area of sociality, nutrition, and eHealth literacy.

## Introduction

Aging brings with it some chronic conditions, along with the reduction of some functions, (1–3) which can lead to a loss of autonomy and frailty. The care of older adults with a loss of autonomy is therefore becoming a major social, medical, and economic issue due to the insufficient number of family or professional carers, enabling older adults to live at home as long as possible and delay entry to institutionalization (4). However, aging is not the same for all individuals. It is dependent on many factors such as genetic factors that cannot be modified and environmental factors including lifestyle (5). It is on the latter that preventive actions can be carried out throughout life (1). In addition to preventive action, the development of new care solutions is important (6), to reduce or minimize the consequences of these age-related diseases, support the health system, and promote active and healthy aging.

## Background

Europeans are living longer and longer. According to INED (7) the life expectancy of a European woman is 83.7 years and 78.3 years for a man in 2018. Japan is the country with the highest life expectancy. Women live on average 88.1 years and men live on average 81.9 years (7). However, the increase in life expectancy is not necessarily accompanied by an increase in healthy life expectancy. In Europe, a woman can expect to live in good health for an average of 64.5 years and a man can expect to live in good health for an average of 63.4 years (8).

As people age, some of their cognitive functions deteriorate (9), and they experience psychological and physical (10–12) difficulties. These changes generate an increase in the workload required by both family and health professionals (13, 14). For these reasons, it is necessary to act with a view to prevention, starting with the concept of active aging. Active and healthy aging refers to the maintenance and development of functional abilities that enable older adults to live well (World Health Organization, n.d) in terms of physical, mental, and social health while actively participating in society.

With the emergence of the concept of healthy and active aging and the identification of factors that contribute to the development of age-related diseases and loss of autonomy, health organizations have tried to improve their strategies to prevent these risk factors and diseases (15). Different structures, organizations, or professionals offer prevention services such as physical, cognitive, emotional, or social activities. However, access to private professionals for prevention targeted to individual needs and preferences is expensive, whereas the offer of public organizations is only slightly customizable and may not be accessible to all seniors. This inequality of access is reinforced by the current health context linked to the COVID-19 crisis, which has led to the cessation or postponement of workshops or face-to-face activities in sports and intergenerational or cultural clubs. A number of videoconference activities have been developed over the past years. However, this remote format does not facilitate the personalization of interventions. With the development of technology, new tools have appeared, including virtual coaches, which seem to be of interest in supporting the behavior of individuals. A virtual coach is defined by Siewiorek et al. (16) as a personalized system that continuously monitors the activities and environment of its users. Virtual coaches detect situations where an intervention would be desirable and proposed to the user. To this end, coaches take the form of activity sensors combined with a coaching application located on the Internet, a smartphone, a sensor (17), or a social assistance robot (SAR) (18). Technology plays an important role in the aging process, impacting both individuals and society as a whole. On a personal level, wearable gadgets and health applications keep track of one’s well-being, and telemedicine offerings enhance the availability of healthcare services. At the societal level, health efficiency, data-driven policies, and the development of social platforms connecting users have a positive influence. However, challenges such as equitable digitization and accessibility require attention to ensure a beneficial and inclusive impact, especially considering the skill level of the users of older than 65 years with technology, not only from a user skills perspective but also from a tool acceptance perspective (19, 20). In this regard, several studies have been conducted that quantitatively and qualitatively assess access to the Internet of Things (IoT) among the older adult population (21, 22).

Through a personalized approach, the virtual coaching system can enable people to live a healthy lifestyle, identifying personal needs and goals and providing appropriate risk predictions and individualized recommendations (23, 24). These devices cover a variety of domains and audiences (25). There are a multitude of virtual coaches and apps for the promotion of nutrition (26), physical activity (27), mood, sleep (28), and even more clinical applications, such as rehabilitation (29) or monitoring of cardiovascular pathologies (30).

There are virtual coaches for adults, children with autistic disorders, and older adults. These tools have attracted interest from healthcare organizations and consumers for promoting health, wellness, physical activity, and lifestyle improvement (31). The use of these virtual coaches and apps has great potential to help older adults improve their quality of life by addressing age-related issues and the physical and social implications of aging (32). Moreover, embracing these proactive measures with the assistance of a virtual coach empowers older adults to maintain independence and comfortable living in their homes for an extended period (33). This reduces the need for constant monitoring by health professionals, limits the costs that would otherwise be incurred (32), and helps mitigate the wider impact of demographic aging on healthcare (4).

However, the technologies developed for healthy and active aging have some limitations. Indeed, they are mainly used for short period of time and are poorly integrated into the daily lives of older adults, thus limiting their benefits (6). Moreover, interactions with these technologies are not ideal since they do not lead to realistic and satisfying social interactions due to technologies that are not yet advanced enough (34). It is therefore necessary to design and evaluate new products that consider the needs and preferences of seniors and their relatives for a sustainable and optimal use of these devices (35). The aim is to enable seniors to live independently in their own homes for as long as possible, preventing social isolation and encouraging active participation in social and group activities.

In this context, the creation of an intercultural and customizable virtual coach may represent an effective solution. Through cooperation between European (Italy, France, and Germany) and Japanese partners, the e-VITA project proposes different technological tools that are adapted to older adults and their daily lives, investigating the effect of cultural aspects in accepting technology and how this affects the outcome. In tackling the task of crafting these technological tools, the e-VITA project takes on a comprehensive approach. This involves seeking input from all stakeholders at both the personal and societal levels. By engaging older adults, their informal and professional health caregivers, community members, and policymakers, the project aims to foster collaboration. The insights gained from these consultations are then mapped and utilized to comprehend the contextual use and identify potential users of the system (36, 37). The inclusion of different types of beneficiaries in all the countries could support local governments to adopt and adapt cross-national policies for AHA that fulfill the real needs of older adults, respecting different cultural perspectives. Therefore, the functionalities and services available and proposed are in response to the needs of older adults and concern social relations, physical activities, skills, autonomy, stimulation, communication, and safety.

## The study

### Study setting

The study will be conducted at the Center for Cognitive Disorders and Dementia (CDCD) of the Neurology Unit of the Istituto Nazionale Ricovero e Cura per Anziani IRCCS INRCA, Ancona, Italy. In Germany, the study will be carried out by the Diözesan-Caritasverband für das Erzbistum Köln e.V. (Diocesan Caritas Association for the Archdiocese of Cologne e.V.). In France, the study will be conducted by Hôpital Broca, Paris. In Japan, three institutes will carry out the study, namely, Tohoku University –Smart Ageing Research Center, J.F. Oberlin University, and Misawa Homes Institute of Research and Development Co. Ltd.

### Aim

The research is structured as a randomized controlled trial with the objective of enhancing well-being in older adults, promoting active and healthy aging, contributing to independent living, and mitigating the risks of social exclusion through the utilization of a virtual coach. Participants will be divided into two groups: the experimental group (EG), receiving a virtual coach, a smartphone, and a booklet, and the control group (CG), receiving only a booklet.

Assessments will be conducted at the baseline (T0), midway through the intervention (after 3 months—T1), and at the conclusion of the intervention (after 6 months—T2). The primary aim of the study is to gauge the enhancement of participants’ quality of life (QoL) using EQ 5D 5 L. Additionally, the research will assess the usability, user experience, acceptability, and fulfillment of needs after using the e-VITA system. It will also explore potential changes in various health-related aspects, such as nutrition, loneliness, and health literacy.

### Objectives

The general objective is to improve the well-being of older adults, promote active and healthy aging, contribute to independent living, and reduce risks of social exclusion of 240 healthy older adults recruited from Europe (France, Germany, and Italy) and Japan by making use of a digital tool for personalized virtual coaching support.

### Design/methodology

#### Recruitment

Patients are selected by the Neurology Operating Unit and Rehabilitation Medicine Operating Unit of IRCCS INRCA in the Ancona branch. After a reflection period of 2 weeks followed by reading the information letter and the consent form received by email, the participants who confirmed their wish to participate in the research by writing or orally will be invited by the investigator to consult a doctor during 3 months, preceding the start of the research. The doctor, volunteering to carry out the inclusion visits, will be the first to give the participants an information letter and two consent forms. Once the consent forms have undergone thorough proofreading and received signatures from both the participant and the doctor, the doctor will assess the participant’s eligibility for the research using an anamnesis Clinical Frailty Scale (CFS) (38), Montreal Cognitive Assessment (MOCA) (39), Geriatric Depression Scale (GDS) (40), and Short Physical Performance Battery (SPPB) (41). This comprehensive medical examination, conducted before the commencement of the experiment, will determine whether participants meet the inclusion criteria. Those who have signed the consent form but do not meet the inclusion criteria as confirmed by the doctor will be excluded from the research. The trial is scheduled to commence in May 2023 and is anticipated to conclude in December 2023.

#### Participants

Each European country will enroll 40 subjects.

The inclusion criteria are:

Age ≥ 65 years;Ability to provide informed consent;Able to stand and walk unaided;No acute or untreated medical problems;MoCA ≥22;GDS < 9;SPPB ≥7;Clinical Frailty Scale score between 2 and 4;

For patients with MoCA scores between 22 and 25, an informal caregiver is required to be present during the explanation of the project and the administration of the assessment scales.

The exclusion criteria are:

Failure to meet the inclusion criteria;Use of active implant or non-implant medical devices;Allergy to nickel;Simultaneous participation in other studies;Absence of written informed consent;Occurrence of a myocardial infarction or stroke within the past 6 months;Presence of painful arthritis, spinal stenosis, amputation, painful foot lesions, or neuropathy that significantly limits balance and mobility;Uncontrolled hypertension;Presence of a pacemaker or implantable cardioverter-defibrillator;Advanced Parkinson’s disease or other neuromuscular disorders;Diagnosis of metastatic cancer or undergoing immunosuppressive therapy;Significant visual or hearing impairment.

#### Sample size determination

In the study by Summers et al. (42), the EuroQol 5 dimensions (EQ 5D) was evaluated in two groups of older adults with physical pre-frailty conditions. EQ 5D, a test widely used to measure health status-related quality of life, was used to calculate the sample size. Assuming an overall sample size of 220 subjects (110 cases and 110 controls), 2 repeated assessments (baseline and follow-up), a significance level of 0.05, power of 90%, a correlation among repeated measures of 0.5, and a non-sphericity correction ε of 1 in an ANOVA model within-between interactions, the achieved effect size for this study is 11% (corresponding to a small effect size in a coherent way with the literature). Even factoring in a dropout rate of 10%, the total number needed would be 240 subjects, evenly divided into 120 cases and 120 controls. The hypothesis is that this sample size is more than adequate to detect variations in secondary outcomes. For these secondary outcomes, a treatment effect size is assumed to be similar to or even greater than the one identified for the primary outcome.

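### The detectable effect printed as 11% and called small is Cohen's f = 0.11 for the group-by-time interaction, which is a 0.44 SD between-arm difference in EQ-5D change

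*Protocol article*

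**What the plan says.** All statements are in the protocol article under Sample size determination.

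- Inputs: 220 evaluable people in two equal arms, each measured twice, tested at the 5% level with 90% power. The two measurements are taken to correlate at 0.5. The test is specified with "a non-sphericity correction ε of 1 in an ANOVA model within-between interactions".
- Result: "the achieved effect size for this study is 11% (corresponding to a small effect size in a coherent way with the literature").
- Enrolment: "Even factoring in a dropout rate of 10%, the total number needed would be 240 subjects", split equally between the arms.
- Secondary outcomes: the section hypothesises that "this sample size is more than adequate to detect variations in secondary outcomes", assuming that their effects are at least as large as the primary one.

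The effect-size metric is not named. No EQ-5D difference and no SD is given.

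**The concern.** A percentage with no metric cannot be interpreted, and the word small invites the reader to think of a standardised difference of about 0.2. The trial's question, under Aim and Outcome measures, is how much more quality of life improves with e-VITA than with the booklet. The useful statement is therefore the between-arm difference in change that the design can detect. If that difference is well above 0.2 SD, the section makes the primary comparison look more sensitive than it is, and a null result could be over-read. The same section gives a dropout-adjusted total that does not return its own 220 evaluable subjects.

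**Working it through.** **Inputs** (all from Sample size determination): N = 220 (110 per arm), m = 2 assessments, alpha = 0.05, power 90%, rho = 0.5, epsilon = 1, within-between interaction; dropout 10%; 240 enrolled.

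**1. Reproduce the plan's figure.** For the interaction, lambda = f² x N x m x epsilon / (1 − rho), with 1 and N − 2 degrees of freedom.

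- lambda = 0.0121 x 220 x 2 / 0.5 = 10.648, giving power 0.901.
- The f detectable with exactly 90% power at N = 220 is 0.1098.
- The smallest N that gives 90% power at f = 0.11 is 220.

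The figure reproduces as Cohen's f = 0.11.

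**2. Try other readings of 11% at N = 220.**

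| Reading | Power |
|---|---|
| Standardised difference in change of 0.11 | 0.13 |
| f = 0.11 in a two-group comparison of change scores (difference 0.22) | 0.37 |
| f = 0.11 without the correlation term (lambda = f² x N) | 0.37 |
| Partial eta squared = 0.11 | 0.999 |

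None of these matches 90%.

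**3. Convert f to the treatment contrast.** In a 2 x 2 interaction the cell deviations are +f and −f SD in one arm, and −f and +f SD in the other. One arm changes by −2f and the other by +2f, so the difference in change is 4f = 4 x 0.11 = 0.44 SD.

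The SD of change is SD x √(2(1 − rho)). At rho = 0.5 this equals the raw SD, so 0.44 holds on both scales.

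Cross-check with a two-sample t-test on change scores, 110 per arm: the squared noncentrality is 0.44² x 110/2 = 10.648, the same lambda as in step 1. A simulation of 20,000 trials gave power 0.902.

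**4. Compare with the usual benchmarks.** In a plain two-group comparison f is half the standardised difference, so f = 0.10 corresponds to 0.20 SD. In this interaction f is a quarter of the difference in change, so f = 0.10 corresponds to 0.40 SD, and 0.20 SD corresponds to f = 0.05. Power for a 0.20 SD difference in change:

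- 220 completers: lambda = 0.05² x 220 x 2 / 0.5 = 2.20, power 0.315.
- 216 completers: lambda = 0.05² x 216 x 2 / 0.5 = 2.16, power 0.310.

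**5. Dropout.**

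- 240 x 0.90 = 216, which is 4 short of 220.
- 220 / 0.90 = 244.4, so 245 would be needed, or 246 for equal arms.
- 1 − 220/240 = 8.3%, the dropout that 240 can absorb.
- With 216 completers, power at f = 0.11 is 0.896. The f detectable with 90% power is 0.1108, a difference of 4 x 0.1108 = 0.443 SD.

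**6. Dependence on rho** (216 completers, 90% power, in raw SD). The detectable difference is 0.443 x √(2(1 − rho)): 0.52 at rho = 0.3, 0.44 at 0.5 and 0.34 at 0.7. The values 0.3 and 0.7 are assumed here to show the range.

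**The case against.** **No calculation behind the 220 fails.** This stands. A reader might infer that the sample size is wrong or that enrolment must rise, but the stated inputs return f = 0.11 at exactly N = 220.

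**Small is the nominal label for f near 0.10, and the section never claims to detect 0.2 SD.** This also stands, so the label does not contradict the text. It remains a poor description, because the benchmark's familiar meaning of 0.20 SD belongs to a plain two-group comparison. The contrast this trial tests is 0.44 SD. Calling that moderate would also be a convention, since 0.44 is below the usual medium value of 0.5, so it is better to give the number without an adjective.

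**The plan does not target 0.20 SD.** True. The 31% shows what the word small would imply and is not a shortfall against a stated target. No passage says that a null result would exclude small gains.

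**The Data analysis section adds a regression on change adjusted for potential confounders.** If baseline EQ-5D is one of them (an assumption) and rho = 0.5, the residual SD shrinks by √(1 − 0.25) = 0.866. The detectable difference with 216 completers becomes about 0.443 x 0.866 = 0.38 SD, and power at 0.20 SD is about 39%. The figures improve, but the detectable difference is still nearly twice 0.2.

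**The secondary-outcome sentence is a hypothesis with its condition attached.** A reader might infer that it rests on misreading f. It does not: given effects similar to or larger than the primary one, about 90% power follows whatever adjective is used. What can be criticised is that the size of the assumed effect is not visible to the reader.

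**The dropout gap is trivial.** Agreed. It costs about half a percentage point of power, and 240 is 2% below 245.

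**Conclusion.** The point holds as a misstatement of the detectable effect. The printed 11% is Cohen's f = 0.11 for the interaction. At the stated correlation of 0.5 it means a 0.44 SD between-arm difference in EQ-5D change, more than twice the conventional small difference of 0.2, for which power is about 31%. The dropout total is inconsistent with the section's own 220, but power falls only from 90.1% to 89.6%.

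The result rests on reading the figure as f, the only reading tried that fits 90% power, and on rho = 0.5 and the unadjusted interaction test. Two matters stay open. Without an EQ-5D SD, 0.44 SD cannot be turned into index points, and whether the effect agrees with the cited literature cannot be checked from the document. The documents do not support the stronger conclusion that the trial is wrongly sized. Severity is minor to moderate.

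**What to change.** Replace the effect-size and dropout statements with wording such as: *With 240 randomised and 10% dropout (216 completers), the trial has about 90% power to detect a between-arm difference in EQ-5D change of 0.44 SD (Cohen's f = 0.11 for the interaction, rho = 0.5).*

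Remove the percentage and the word small. In place of the claim of more than adequate size for secondary outcomes, say that adequacy there assumes differences of about 0.44 SD or more on those scales.

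The cost is wording that reads less favourably. Enrolment, allocation, endpoint and analysis stay as they are.

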#### Intervention

The interventions are oriented toward the model of intrinsic capacity (43), and an improvement of the general well-being is to be achieved through the promotion of the different areas. For this study, 240 healthy older adults will be enrolled. Figure 1 illustrates the flowchart, detailing the process of patient selection.

**Figure 1 fig1:**
[figure not shown]
Flowchart of the patient selection.

In total, 120 subjects will be enrolled in the experimental group and will receive the e-VITA platform composed of a virtual coach, several sensors for monitoring, and a smartphone to use at home.

The control group will receive only the booklet with nutritional, cognitive, and physical suggestions.

